# 5. Registration and Allocation

## 5.1. Registration Procedure

After confirming that the patient meets all inclusion criteria and does not meet any exclusion criteria, informed consent will be obtained. The required information will then be entered and registered in the Electronic Data Capture (EDC) system managed by the Cancer Institute Hospital.

EDC system: Viedoc

URL：https://v4jp.viedoc.net/Login

Contact information for patient registration and inquiries regarding patient

selection criteria]

### 5.1.1. Notes on registration

Registration after the initiation of protocol treatment is strictly not permitted under any circumstances. If the entered data are incomplete, registration will not be accepted until all required information is provided. Registration is considered complete when a registration number is issued. Except in cases where consent is withdrawn, including refusal for research data usage, once a patient is registered, the registration cannot be cancelled or deleted from the database. In the event of duplicate registration, the initial registration information (registration number and assigned group) will be used in all cases. If erroneous or duplicate registrations are discovered, promptly notify the research secretariat.

## 5.2. Randomization and Randomization Factors

After registering a case in the EDC system, the patient will be randomly assigned to one of the groups by the EDC system. The allocation factors are surgical time (≥ 560 min or < 560 min) and HbA1c value (HbA1c < 6.0 or 6.1-6.4), which are factors of particular concern that may impact the primary outcome. The minimization method will be used to ensure that significant imbalances do not occur. Details of the allocation factors will remain blinded to the patients.

# 6. Treatment plan and Criteria for Treatment Modification

## 6.1. Protocol Treatment

### 6.1.1. Enteral Nutrition Used:

After esophagectomy, the control group will receive Meiji Main as the enteral nutrition formula, while the intervention group will receive Glucerna®-REX.

### 6.1.2. Dosing Schedule and Dosage

Starting from postoperative day 1, the control group will receive the standard enteral formula Meiji Main, while the intervention group will receive the glucose-restricted enteral formula Glucerna®-REX. Both formulas will be continuously administered for 24 hours at the following doses: 400 mL on postoperative day 1, 800 mL on day 2, 1200 mL on day 3, and 1600 mL from day 4 onwards. From postoperative days 4 to 8, the administration will continue at 1600 mL. On postoperative day 9, both groups will transition to standard postoperative management, switching to the concentrated liquid formula HineX® E-gel at 1000 mL, and initiate oral intake.

### 6.1.3. Blood Glucose Management

In this study, after the patient returns to the ward immediately post-surgery, the sub-investigator will attach the FreeStyle Libre Pro to the outer upper arm of the patient and begin continuous glucose monitoring (CGM). The sub-investigator will remove the FreeStyle Libre Pro from the patient on postoperative day 9. In addition, from the time the patient returns to the ward, blood glucose will be routinely measured 4 times a day using either blood gas analysis or the Dexter system.

Rescue treatments for hyperglycemia and hypoglycemia will be managed based on the blood glucose values obtained from the routine measurements via blood gas analysis or the Dexter system. Blood glucose information obtained from the FreeStyle Libre Pro will not be used as a reference for determining whether to perform rescue treatments for hyperglycemia or hypoglycemia.

Rescue treatments for hyperglycemia and hypoglycemia will be conducted as described below. However, rescue treatment for blood glucose levels between 201-299 mg/dL will not be permitted until the second postoperative day.

Criteria for rescue treatment for postoperative hyperglycemia and hypoglycemia

| Blood glucose (mg/dL) | | season | Fast-acting insulin | 50% Dextrose |
| --- | --- | --- | --- | --- |
| Hyperglycemia | 201 or more ~ 249 or less | Up to postoperative day 2 | None | - |
|  |  | From the 3rd postoperative day onwards | 2 Units | - |
|  | 250 or more ~ 299 or less | Up to postoperative day 2 | None | - |
|  |  | From the 3rd postoperative day onwards | 4 Units | - |
|  | 300 or more ~ 349 or less | Postoperative day 1 and beyond | 6 Units | - |
|  | 350 or more ~ 399 or less | Postoperative day 1 and beyond | 8 Units | - |
|  | 400 or more | Postoperative day 1 and beyond | 10 Units | - |
| hypoglycemia | 69 or less | Postoperative day 1 and beyond | - | 20mL |

<Rationale for rescue treatment for hyperglycemia and hypoglycemia>

Given that the study targets non-diabetic patients and the primary endpoint is the average TIR up to postoperative day 2, non-intervention with rapid-acting insulin will be permitted for blood glucose levels between 201 mg/dL and 299 mg/dL during this period. Conversely, if blood glucose levels fall below 69 mg/dL or exceed 300 mg/dL before postoperative day 2, non-intervention may pose a significant risk to patient safety. In such cases, intervention will be conducted using glucose administration or rapid-acting insulin, as appropriate.

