### 2.2.2. Blood Glucose Monitoring and Management

During the Intensive Care Unit (ICU) stay, blood glucose levels are measured every 6 hours using arterial blood gas samples collected via the arterial line inserted into the radial artery. From postoperative day 4 onwards, while in the general ward, intermittent blood glucose measurements using finger-prick tests (typically four times a day: before each meal and before bedtime) are conducted if intervention is deemed necessary based on prior blood glucose trends.

Interventions for blood glucose levels (rescue treatment for hyperglycemia and hypoglycemia) are as follows:

| Blood glucose (mg/dL) | | Fast-acting insulin | 50% Dextrose |
| --- | --- | --- | --- |
| Hyperglycemia | 201 or more ~ 245 or less | 2 Units | - |
|  | 250 or more ~ 299 or less | 4 Units | - |
|  | 300 or more ~ 349 or less | 6 Units | - |
|  | 350 or more ~ 399 or less | 8 Units | - |
|  | 400 or more | 10 Units | - |
| hypoglycemia | 69 or less | - | 20mL |

Postoperative management of the current situation in our department

| Location  Days  Items | operating room | ICU | | | General Ward | | |
| --- | --- | --- | --- | --- | --- | --- | --- |
|  | Day0 | Day1 | Day2 | Day3 | Day4-8 | Day9 | Day 10 onwards |
| Surgery | ○ |  |  |  |  |  |  |
| Meiji Main |  | 400mL | 800mL | 1200mL | 1600mL |  |  |
| Hynex ® Eagle |  |  |  |  |  | 1000mL | Tapering as appropriate |
| Dietary intake |  |  |  |  |  | ○ | ○ |
| Blood glucose measurement (4 times/day) |  | ○ | ○ | ○ | ○ | ○ | ○ |
| Interventions for blood glucose levels |  | ○ | ○ | ○ | ○ | ○ | ○ |

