### 2.5.2. Expected Burden and Disadvantages

The study will use Glucerna®-REX, Meiji Main, and FreeStyle Libre Pro, which are all widely used in routine clinical practice, as outlined in Section 2.1. Glucerna®-REX and Meiji Main will be provided as dietary components, and both the sensor and Reader for the FreeStyle Libre Pro will be purchased using the esophageal surgery research fund. Therefore, participating in this study will not impose any additional physical burden or economic disadvantage on the patients.

According to the study protocol, the frequency and parameters of blood tests will not exceed those of standard postoperative management. However, there is a slight risk of skin irritation or inflammation around the application site due to the adhesive used when attaching the FreeStyle Libre Pro sensor.

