## 6.3. Combined treatment and supportive treatment

### 6.3.1. Acceptable combination and supportive care for hyperglycemia and hypoglycemia

Rescue treatments for hyperglycemia and hypoglycemia (as outlined in Section 6.1.3 Blood Glucose Management) are the only interventions permitted.

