### 6.3.2. Unacceptable Concomitant and Supportive Therapy

There are no prohibited concomitant therapies or supportive treatments..

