## 8.2. Evaluation items on the day of surgery

1. Surgery Information
2. Allocation
3. FreeStyle Libre Pro attachement
4. 24-hour continuous glucose monitoring
5. Confirmation of Survival

## 8.3. Evaluation Items on Postoperative Day 1

1. Conformation of FreeStyle Libre Pro Continues
2. 24-hour continuous glucose monitoring
3. Blood glucose measurement 4 times a day with blood gas
4. Continuous administration of 400 mL of enteral nutrition (Meiji Main and Glucerna®-REX)
5. If necessary, the rescue of insulin for hyperglycemia and hypoglycemia
6. Presence or absence of postoperative infectious complications
7. Presence or absence of other complications
8. Adverse events
9. Confirmation of survival or death

## 8.4. Evaluation Items on Postoperative Days 2 to 3

1. Conformation of FreeStyle Libre Pro Continues
2. 24-hour continuous glucose monitoring
3. Blood glucose measurement 4 times a day with blood gas
4. Continuous administration of enteral nutrition (Meiji Main and Glucerna-REX ®) (postoperative day 2; 800 mL, postoperative day 3: 1200 mL)
5. If necessary, the rescue of insulin for hyperglycemia and hypoglycemia
6. Presence or absence of postoperative infectious complications
7. Presence or absence of other complications
8. Adverse events
9. Confirmation of survival or death

## 8.5. Evaluation Items on Postoperative Days 4 to 8

1. Conformation of FreeStyle Libre Pro Continues
2. 24-hour continuous glucose monitoring
3. Blood glucose measurement 4 times a day with dexter
4. Continuous administration of enteral nutrition (Meiji Main and Glucerna-REX ®) (postoperatively 4 days or later; 1600 mL)

Dosage may be changed or enteral nutrition may be changed depending on the patient's condition (e.g., adverse events) (see 6.2.3.)

1. If necessary, the rescue of insulin for hyperglycemia and hypoglycemia
2. Presence or absence of postoperative infectious complications
3. Presence or absence of other complications
4. Adverse events
5. Confirmation of survival or death

## 8.6. Evaluation Items on Postoperative Day 9

1. Remove the FreeStyle Libre Pro. (Postoperative 1~Collection of blood glucose data on day 8)
2. Enteral nutrition: Change of administration to Heinegel (change timing can be changed depending on the patient's condition)

However, if Meiji Main and Glucerna-REX ® are still administered after the 9th postoperative day, until the end of administration

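### Section 2.5.2 omits that the trial withholds rescue insulin at 201-299 mg/dL through POD 2, and section 6.1.3 words that rule both as binding and as optional

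*Protocol*

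**What the plan says.** Protocol section 6.1.3 sets the trial's rescue rule. Its text says that "rescue treatment for blood glucose levels between 201-299 mg/dL will not be permitted until the second postoperative day", and its table has the row "201 or more ~ 249 or less | Up to postoperative day 2 | None", with insulin in that band starting on POD 3. The rationale under the table then says that "non-intervention with rapid-acting insulin will be permitted for blood glucose levels between 201 mg/dL and 299 mg/dL during this period".

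Three other places bear on the same rule:
- Section 6.3.1 says that the rescue treatments of 6.1.3 "are the only interventions permitted".
- The section on unacceptable concomitant therapy (the second one numbered 6.3.2) says: "There are no prohibited concomitant therapies or supportive treatments".
- The evaluation items for POD 1 (8.3) and for POD 2 to 3 (8.4) list "If necessary, the rescue of insulin for hyperglycemia and hypoglycemia", with no glucose threshold.

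Usual practice is in section 2.2.2. Its table begins with "201 or more ~ 245 or less | 2 Units", and the calendar below it marks glucose intervention from Day 1. On risk, section 2.5.2 concludes that "participating in this study will not impose any additional physical burden or economic disadvantage on the patients", and then names skin irritation or inflammation at the sensor site as the only risk.

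**The concern.** There are two linked faults.

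**Risk statement.** Withholding insulin at 201-299 mg/dL through POD 2 is a change from the department's own practice, and it applies to every participant in either arm. Section 2.5.2 does not mention it. Section 2.1 offers the infection risk of early hyperglycaemia as the reason for the trial, so by the protocol's own argument this is not a trivial omission. A review board that relies on 2.5.2 would miss the main way in which glucose care differs from routine.

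**Rule wording.** The primary endpoint is the share of 48 hours spent at 70-180 mg/dL (11.3), so all of the 201-299 band counts as out of range. The trial is open-label (2.4). A rule followed identically in both arms does not bias the comparison. A rule read as optional can, because whoever decides on insulin knows the formula. Insulin given more often in the arm with higher glucose would pull the difference toward zero.

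**Working it through.** **1. The passages side by side (201-299 mg/dL, POD 1-2)**

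| Place | Content | Reads as |
|---|---|---|
| 6.1.3 text | rescue not allowed | binding |
| 6.1.3 table | none up to POD 2, insulin from POD 3 | binding |
| 6.1.3 rationale | leaving the patient untreated is allowed | optional |
| 6.3.1 | only the 6.1.3 rescue | binding, by reference |
| 6.3.2 (unacceptable therapy) | nothing prohibited | general; sits badly with 6.3.1 |
| 8.3 and 8.4 | insulin if needed, no threshold | open |
| 2.2.2 (usual care) | insulin from 201 mg/dL, from Day 1 | differs from the trial rule |

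The limits also vary. On days, the 6.1.3 text says *until* POD 2, the table *up to* POD 2, and the rationale *before* POD 2 for the safety triggers. On glucose, the rationale acts below 69 and above 300, whereas the 6.1.3 table and section 6.2.2 act at 69 or less and at 300 or more. The values 69 and 300 themselves are therefore treated differently.

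**2. What would record insulin given at 201-299 on POD 1-2**

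Discontinuation item 5 in 6.2.2 and secondary endpoint 12 both start at 300 mg/dL. The per-protocol set excludes significant protocol violations (11.1), but that works only if the protocol settles whether such insulin is a violation.

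**3. The protocol's own infection data (2.1)**

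In non-diabetic patients, infections occurred in 42.9% with a POD 1 mean of at least 200 mg/dL and in 25.2% below it, a difference of 42.9 - 25.2 = 17.7 percentage points. The multivariate ratios are 1.94 for POD 1 and 3.68 for POD 2. These are retrospective associations with a daily mean. They do not show what withholding insulin after a single reading does.

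**4. The planned precision**

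Inputs from 11.6: 48 patients (24 per group), SD 8.5 points, read as the per-patient SD in each group.

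- SE = 8.5 × √(1/24 + 1/24) = 2.45
- Half-width, normal quantile: 1.96 × 2.45 = 4.81
- Half-width, t quantile with 46 df: 4.94

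Both match the stated ±5. One hour of 48 is 100/48 = 2.08 TIR points, so 4.94 points is 4.94/100 × 48 = 2.37 hours.

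**5. Possible shift in the primary difference (intervention minus control)**

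Shift = -(share treated in control - share treated in intervention) × hours gained / 48 × 100. The documents give neither the shares nor the hours; all are assumptions.

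| Control treated | Intervention treated | Hours gained per treated patient | Shift (points) | Fraction of 4.94 |
|---|---|---|---|---|
| 20% | 10% | 2 | -0.42 | 0.08 |
| 30% | 10% | 4 | -1.67 | 0.34 |
| 50% | 20% | 8 | -5.00 | 1.01 |

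A still more lopsided assumption (50% against 0%, 8 hours) gives -8.33, which shows that the upper end is set by the assumptions and not by the documents. If insulin went mainly to the intervention arm, the sign would reverse.

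**The case against.** The strongest reply is that 6.1.3 does give a clinician an instruction. The rule and its table agree, and the softer sentence stands in a rationale and may be loose translation. The table also settles the day limit, since it ends the restriction with POD 2 and resumes insulin on POD 3. That is largely right. A reader might infer from *until* that the status of POD 2, half of the primary window, is undecided; read with the table, it is not.

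A reader might also take the section on unacceptable therapy as a third rule that leaves insulin unrestricted. Section 6.3.1 deals with glucose specifically and limits treatment to 6.1.3, so this is an untidy general sentence and not a third rule.

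On risk, the reply is that 6.1.3 states the withholding openly with its reason and safety limits, that 7.1.1 lists hyperglycaemia as an expected event, and that 13.2.1 requires possible disadvantages to be explained. All true. It is also true that 2.5.2 does not claim that glucose care equals usual care; its comparison with standard management covers blood tests only. The fault is an omission beside a statement of no added burden. A reader might go further and conclude that patients are told the wrong risk. The consent text is not available, so that cannot be established.

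On recording, the general provisions on deviations and the handling of cases before data fixation (11.1) exist, and detailed classification may be left to the SAP. But no later classification can be clean while the protocol text says both that such insulin is barred and that withholding it is optional.

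**Conclusion.** Wrong as written, on two counts. First, section 2.5.2 is contradicted by 2.2.2 and 6.1.3 read together: the trial withholds insulin that routine care gives, and the risk section omits this although 2.1 associates early hyperglycaemia with infection. Second, the 6.1.3 rule and its rationale conflict on whether withholding is required, and 6.3, 8.3, 8.4 and the differing limits add to the uncertainty.

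The first conclusion rests on the text alone. For the second, bias in the primary TIR is possible but its size cannot be derived. The illustrated shifts of about 0.4 to 5 points assume arm-specific insulin use and hours gained that appear nowhere in the documents. A reader might infer a bias as large as the planned ±5; among the three scenarios tabulated only the most extreme reaches it, and nothing in the documents makes that scenario likely.

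**What to change.** - Reconcile the 6.1.3 text, table and rationale, 6.3.1, the section on unacceptable therapy, and 8.3 to 8.4 into one statement, with one day limit and one set of glucose limits that also match 6.2.2. Which clinical rule applies is for the investigators; none is proposed here.
- State that insulin given outside that rule on POD 1-2 is recorded as a deviation, with the glucose value and time, and reported by arm.
- Correct 2.5.2 so that it says how glucose management in the trial differs from 2.2.2, and check that the consent text agrees.

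Cost: protocol wording, one deviation item in data capture if it is not already there, and submission of the changed risk text (and the consent text, if it is affected) to the review board. The sample size and the primary analysis do not change.

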## 6.2. Criteria for Protocol Treatment Completion, Discontinuation, or Modification

### 6.2.1. Definition of Protocol Treatment Completion

The initiation of protocol treatment is defined as the application of the FreeStyle Libre Pro. The protocol treatment is considered complete when the administration of Meiji Main, Glucerna®-REX, or any other nutritional formula is finished and the FreeStyle Libre Pro is removed.

If Meiji Main, Glucerna®-REX, or any other nutritional formula is administered up to postoperative day 8 and the FreeStyle Libre Pro remains attached until postoperative day 9, the protocol treatment is deemed complete

.

### 6.2.2. Criteria for Protocol Treatment Discontinuation

Protocol treatment will be discontinued in any of the following situations. The date of protocol treatment discontinuation will be defined as the date of death in the event of death or the date on which the attending physician determines that protocol treatment should be discontinued for other reasons.

When it becomes difficult to continue the study due to adverse events.

1. If the patient offers to discontinue protocol treatment.
2. Death during protocol treatment
3. When it is determined that discontinuation is necessary at the discretion of the principal investigator or co-investigator.
4. During the ICU period (within 4 days after surgery), the sensor is removed and the missing data is revealed.
5. By the second postoperative day, hyperglycemia (300 mg/dL or more) requiring insulin administration.
6. By the second postoperative day, the patient has a hypoglycemic condition (69 mg/dL or less) that requires sugar administration.
7. Skin troubles attributed to the FreeStyle Libre Pro sensor adhesive.
8. The need arises to remove the seal on the FreeStyle Libre Pro sensor for an MRI examination.
9. In addition, if serious deviations from the protocol are discovered, such as protocol violations, post-registration surgical procedures, or changes in treatment policies.

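### Section 6.2.2 makes three sensor-only events mandatory reasons to end protocol treatment without saying that the allocated feed continues; on its natural reading, the 6.3-day rule in 11.2 shuts out the ICU sensor losses that trigger it

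*Protocol*

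**What the plan says.** Section 6.2.2 opens with "Protocol treatment will be discontinued in any of the following situations". As numbered there, three of the situations concern the sensor alone:

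- item 4: "During the ICU period (within 4 days after surgery), the sensor is removed and the missing data is revealed"
- item 7: "Skin troubles attributed to the FreeStyle Libre Pro sensor adhesive"
- item 8: "The need arises to remove the seal on the FreeStyle Libre Pro sensor for an MRI examination"

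Section 6.1, headed Protocol Treatment, begins with the two formulas: "After esophagectomy, the control group will receive Meiji Main as the enteral nutrition formula, while the intervention group will receive Glucerna®-REX". Section 6.2.1 starts protocol treatment at sensor application and ends it when the study formula "or any other nutritional formula is finished and the FreeStyle Libre Pro is removed". It adds that if feeding of any kind has run to POD 8 and "the FreeStyle Libre Pro remains attached until postoperative day 9, the protocol treatment is deemed complete".

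On glucose safety, section 6.1.3 says: "Blood glucose information obtained from the FreeStyle Libre Pro will not be used as a reference for determining whether to perform rescue treatments".

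Section 11.2 plans a sensitivity analysis where the sensor detaches during the ICU stay. It takes cases whose data, from attachment to detachment, cover at least 70% of the planned measurement days, given as 6.3 days. Section 11.3 defines the primary endpoint over 48 hours.

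**The concern.** Adhesive skin trouble and an MRI are reasons to take a sensor off. They are not reasons to stop an enteral formula, and stopping it serves no purpose the protocol states:

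- **Safety.** CGM values may not guide rescue treatment, and glucose is measured four times a day by other means (6.1.3).
- **Primary endpoint.** Its window closes after POD 2, whereas item 4 runs to day 4 and items 7 and 8 have no time limit.
- **CGM secondary endpoints (5-10).** These need the sensor to POD 8, but stopping the feed recovers none of the lost readings.

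At stake is exposure to the allocated formula after the event, for endpoints that need the feed and no sensor: infectious and overall complications (1-3) and nutritional indicators (11). Staff facing the same sensor loss could also act differently, since the text does not say which formula is then given.

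The second matter is separate. A sensitivity analysis triggered by early sensor loss should be able to include patients with early sensor loss, and the stated threshold appears to rule them out.

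**Working it through.** **1. Does the wording reach the feed?** The list in 6.2.2 is mandatory. The clause on the attending physician's determination fixes the date of discontinuation; it does not make the list optional. Section 6.1 puts the formula within protocol treatment. Section 6.2.3 governs formula changes, but only for adverse events related to the formula. Section 13.2.3 keeps follow-up going after a patient refuses further treatment, but does not say what is fed. No section says the allocated feed continues after a sensor-only event.

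**2. Exposure at risk if the feed did stop.** Daily volumes are from 6.1.2.

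- Planned POD 1-8: 400 + 800 + 1200 + 5 × 1600 = 10,400 mL per patient
- Not given if stopped at the end of POD 2: 9,200 / 10,400 = 88.5%
- At the end of POD 3: 8,000 / 10,400 = 76.9%
- At the end of POD 4: 6,400 / 10,400 = 61.5%

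The protocol gives no event rate. Assume 5-10% for the three events together, so 0.05 × 25 = 1.25 to 0.10 × 25 = 2.5 patients per arm. Planned volume per arm is 25 × 10,400 = 260,000 mL.

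| Feed stopped at end of | Volume lost per arm (mL) | Share of arm |
| --- | --- | --- |
| POD 2 | 11,500-23,000 | 4.4-8.8% |
| POD 3 | 10,000-20,000 | 3.8-7.7% |
| POD 4 | 8,000-16,000 | 3.1-6.2% |

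For scale, section 2.1 reports 127/430 = 29.5% infectious complications. With 30% in both arms of 25, the 95% half-width for the difference is 1.96 × √(2 × 0.3 × 0.7 / 25) = 0.254, about ±25 percentage points. The lost exposure is small against that.

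**3. The 11.2 threshold.** The stated figure reproduces as 0.70 × 9 = 6.3 days, the 9 days running from attachment on the day of surgery to removal on POD 9. The endpoints themselves use POD 1-8, for which 0.70 × 8 = 5.6 days.

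Item 4 of 6.2.2 puts the ICU period within 4 days after surgery; sections 2.2.2 and 8.9 place the ICU on days 1-3. The longest attachment-to-detachment span is therefore 4 days, or 5 if the day of surgery counts as a full day.

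| Base | Required | 4 days of data | 5 days of data |
| --- | --- | --- | --- |
| 9 days | 6.3 days | 44.4% | 55.6% |
| 8 days | 5.6 days | 50% | 62.5% |

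Every entry is below 70%. On the 48-hour primary window, the same 70% would be 0.70 × 48 = 33.6 hours.

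**The case against.** **On the feed.** Protocol treatment can be read as a status label. Section 6.2.1 starts it at sensor application and lets it be complete on another formula, so items 4, 7 and 8 may only record that the feed-plus-CGM package cannot be completed. Section 8.5 ties formula changes to the patient's condition and 6.2.3. Section 8.6 removes the sensor on POD 9 yet allows a study formula to continue beyond it. Section 7.3 counts adverse-event follow-up from the end of feeding. This is one department, and section 16.2 provides memoranda to settle interpretation.

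Much of this stands, so a reader should not infer that the protocol plainly orders the feed to stop. It does not remove the ambiguity: 8.6 deals with feeding past the planned end, not with early sensor loss, and nothing limits the mandatory list to CGM.

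A reader might also infer that lost exposure would fall mainly on the Glucerna-REX arm, because Meiji Main is the department's usual formula (2.2.1). The protocol names no formula to follow a sensor-only discontinuation, so this is conjecture.

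**On 11.2.** It is tempting to say the rule can never be met. That goes too far. Section 11.2 speaks of the ICU stay without repeating the 4-day limit, so a patient kept in the ICU beyond about 6.3 days could qualify. The sentence might also mean that all patients are restricted to those with 70% coverage, and then the set is not empty. Nor does 11.2 tie 6.3 days to the primary endpoint, and a separate 48-hour rule may properly sit in the SAP, so its absence is no defect. What remains is that, on the natural reading and the planned ICU schedule, the cases that trigger the analysis cannot enter it.

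**Conclusion.** Both parts hold as matters of wording with limited consequence.

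Read literally, 6.2.2 ends randomised feeding for a measurement failure and gains nothing by it; the milder reading is possible but not stated. For an affected patient the loss would be large (77% of planned volume if the feed stopped at the end of POD 3). Across an arm it is small: 3.1-8.8% over the range examined, resting entirely on an assumed 5-10% event rate.

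There is no support for inferring bias in the main result. The primary estimate is essentially unaffected by events from POD 3. The main analysis uses the FAS, and discontinuation by POD 2 by itself removes a patient only from the PPS (11.1).

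The 6.3-day rule fails for sensors lost for good within the ICU period as 6.2.2 defines it, whether 8 or 9 days is the base. Only one sensitivity analysis is touched.

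**What to change.** - **6.2.2:** make items 4, 7 and 8 reasons to end CGM only. Add one sentence: the allocated feed and scheduled follow-up continue unless another criterion in 6.2.2 or 6.2.3 applies.
- **6.2.1:** define completion of feeding independently of the sensor staying on until POD 9.
- **Data capture:** record sensor end and feed end as separate items.
- **11.2:** for the primary endpoint, apply the 70% rule to the 48-hour window (33.6 hours). Keep a 70% rule on planned days only for the POD 1-8 averages, apply it to all patients, and state the base (5.6 days of 8, or 6.3 of 9).

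The cost is wording in three sections and one added EDC field, with no new procedures, visits or patients.
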